## Abstract

**Introduction:**

Early and lifelong treatment is essential in patients with familial hypercholesterolaemia (FH) due to genetically elevated low-density lipoprotein cholesterol (LDL-C) from the first years of life. In women with FH, lipid-lowering treatment is interrupted during childbearing years due to contraindication of the medication during conception, pregnancy and breastfeeding. However, little is known about the impact of breastfeeding on lipid profile and other risk markers for atherosclerotic cardiovascular disease (ASCVD) in women with FH compared with women without hypercholesterolaemia, and to what extent statins transfer into breast milk.

We aim to investigate (1) the association between breastfeeding and serum lipid profile in women with and without FH; (2) the association between breastfeeding and other ASCVD risk markers in women with and without FH and (3) the concentration of statins in breast milk of women with FH.

**Methods and analysis:**

FH-FEMINA is a prospective study aiming to include 50 women with FH in Norway, the Netherlands and the Czech Republic. Additionally, 20 women without hypercholesterolaemia will be enrolled as a control group in Norway. Women will be included at the first study visit in gestational week 36, and follow-up visits will be scheduled at 2–4 weeks, and at 3, 6, 9 and 12 months postpartum. Information on lifestyle factors, treatment history and current and previous pregnancies will be collected. At each visit, a non-fasting blood sample, breast milk sample and information on diet, body mass index and blood pressure will be collected. Additional blood samples will be collected from the women with FH at 2, 4, 5, 7, 8, 10 and 11 months postpartum for as long as they are breastfeeding. At (re-)initiation of statin treatment, breast milk samples from women with FH will be collected for drug concentration measurements.

**Ethics and dissemination:**

Ethical approval will be obtained prior to study start in all three countries. Participants will be informed about the study and receive ample time to ask questions before the informed consent form is signed. The findings from this study will be disseminated to healthcare professionals, researchers and patients via peer-reviewed scientific article(s), conferences, patient organisations and social media.

**Trial registration number:**

NCT05367310.

STRENGTHS AND LIMITATIONS OF THIS STUDYA strength of the study is the use of repeated measurements to enable close monitoring of the lipid level variations in women with and without familial hypercholesterolaemia (FH) during the first year postpartum.Another strength is the well-characterised FH diagnosis, which is genetically verified (for most of the participants) or clinically diagnosed.A limitation of the study is the small sample size, reflecting the limited availability of pregnant women with FH within the timeframe of this study.The absence of control group in two of the three countries is a limitation.Variability in breastfeeding practices (frequency, duration) is another limitation that may influence the lipid levels in the first year postpartum.

## Introduction

 Patients with familial hypercholesterolaemia (FH) have genetically elevated levels of low-density lipoprotein cholesterol (LDL-C) from the first years of life. The lifelong cholesterol burden throughout life defines the risk of atherosclerotic cardiovascular disease (ASCVD).^1 2^

In female patients with FH, lipid-lowering treatment is discontinued during childbearing years due to contraindication of the medication during conception, pregnancy and breastfeeding.^3^ Additionally, cholesterol levels increase as part of the normal physiological changes during pregnancy.^4 5^ This pregnancy-related relative increase in LDL-C is similar between women with and without FH, ranging from approximately 30% to 50%.^6^ However, the absolute LDL-C levels at the end of pregnancy are considerably higher in women with FH (mean 8.6 mmol/L) compared with women without FH (mean 3.9 mmol/L).^6^

In a previous study among 80 women with FH from Norway and the Netherlands, using a self-reported questionnaire, we observed a median total duration of pregnancy-related off-statin periods of 2.3 years, from the planning phase of the first pregnancy to the end of breastfeeding of the last child.^7^ However, there were large individual variations, with off-treatment periods ranging from 0 to 14 years. Women with a higher number of children had a longer total duration without lipid-lowering treatment, and 20% of the participants had pregnancy-related off-statin time of more than 4 years. Almost 90% of the women wished to receive more information from healthcare professionals on pregnancy and breastfeeding regarding FH, especially from their general practitioner (GP).^7^

Few, if any, studies on the effects of breastfeeding in women with FH exist. Studies in the general population show that breastfeeding has several benefits for both the mother and the child.^8^ Maternal benefits may include facilitating postpartum weight loss and improving lipid profile.^8 9^ There are also studies indicating that breastfeeding can reduce the risk of type 2 diabetes and cardiovascular disease in women who have breastfed.^8 10^

WHO recommends exclusive breastfeeding for the first 6 months, followed by continued partial breastfeeding up to 2 years of age or longer.^11^ Regarding FH, current guidelines for the management of dyslipidaemias do not provide specific recommendations regarding breastfeeding. Thus, women with FH are usually recommended to follow the same guidelines as those for women without FH.

LDL-C levels decrease postpartum; however, little is known about when and how rapidly the cholesterol levels decrease during breastfeeding in women with FH compared with women without FH. Moreover, the knowledge on the transfer of statins into breast milk is scarce. Some case studies have observed the presence of rosuvastatin and atorvastatin in breast milk; however, the concentrations were low, and the infant exposure was thus assumed to be low.^12^,^14^ More studies on the concentration of statins in breast milk are therefore needed.

In this study, we aim to increase the knowledge on the lipid profile during breastfeeding in women with and without FH, and the concentration of statins in breast milk.

## Methods and analysis

### Study aims

The overall aim of the FH-FEMINA study is to investigate the change in lipid profile in the first year postpartum in women with and without FH. We will also investigate the association between breastfeeding and other cardiovascular risk markers, as well as the concentration of statins in breast milk.

### Primary outcome

In women with FH compared with women without hypercholesterolaemia, we will investigate

The change in serum lipid profile (total cholesterol, LDL-C, high-density lipoprotein cholesterol (HDL-C), triglycerides, lipoprotein(a)) from 2 to 4 weeks post partum up to 12 months postpartum (absolute and relative change).

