### Outcomes

#### Medical history, lifestyle factors and clinical examinations

At the first study visit, information on medical history, including FH diagnosis (age, genetic/clinical), lipid-lowering treatment history, untreated lipid levels prior to pregnancy, use of other medication and dietary supplements, history of current and previous pregnancies, lifestyle factors (physical activity, diet and smoking) and education level, will be collected. At all main study visits (table 1), information on delivery and any complications during pregnancy or delivery, breastfeeding status (yes/no, exclusive/partial, and frequency), BMI and blood pressure are collected. Dietary data are collected at the end of pregnancy and 12 months post partum using a digital food frequency questionnaire to capture the habitual diet during pregnancy and breastfeeding. Dietary data are also collected at all main study visits using a 24-hour dietary recall interview or questionnaire to capture detailed information on the diet the days prior to the blood sample. Weight and length of the child will be collected at the main study visits. At the additional visits, breastfeeding status and frequency, and self-reported maternal weight will also be collected (table 1).

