#### Breast milk samples

Breast milk samples will be collected at the main study visits (table 1) for as long as the women are breastfeeding. Main outcome measures in the breast milk samples are lipid profiling (lipidomics) and metabolite profiling (metabolomics).

If the women with FH (re)-start lipid-lowering treatment (eg, statin) while still having breast milk production, additional breast milk samples will be collected. This breast milk sampling will be standardised by collecting the breast milk samples on days 0, 1, 2 and 3 after statin initiation. For day 0, 1 and 2, a single breast milk sample is collected between 06:00-12:00. On day 3, when the statin is expected to have reached a steady state in breast milk, multiple breast milk samples will be collected at 0, 2, 5 and 12 hours after intake of the statin pill. For all breast milk samples, the participants are asked to pump one breast from full to empty. The concentration of statins will be measured in these breast milk samples. We expect to collect fewer breast milk samples from this time point as it may be challenging to synchronise the initiation of lipid-lowering treatment with the end of breastfeeding.

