### Safety plan

A 30–50% increase in cholesterol levels during pregnancy is normal and expected, but there is limited knowledge available about when and how fast the cholesterol levels decrease after delivery. Women are not routinely monitored during the breastfeeding period. Therefore, the GP or treating physician at a lipid clinic of the women with FH will be informed about the participant’s lipid levels (total cholesterol, LDL-C, HDL-C and triglycerides) from the blood sample taken at 9 months postpartum (V9) to ensure that the GP or treating physician will evaluate further treatment for the woman.

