### Sample size calculation

Sample size calculation for comparing the difference between the two groups (women with FH and control women without hypercholesterolaemia) in changes from 2 to 4 weeks to 6 months postpartum was performed for LDL-C (mmol/L) with 5% significance level and 80% power. Based on the experiences from previous studies, availability of pregnant women and motivation to participate, the project group does not find it realistic to include more than 50 women with FH and 20 control women, that is, a ratio of 2.5 between the sample sizes.

Amundsen *et al*^6^ studied changes during pregnancy in women with FH (n=22) and women without hypercholesterolaemia (n=149). Mean LDL-C in gestational week 36 in the two groups was 8.6 and 3.9, mmol/L, respectively. In the women with FH, mean LDL-C at 3–6 months post partum was 7.0 (n=17), that is, mean change of 1.6 mmol/L, but no information was given about postpartum LDL-C values in the women without hypercholesterolaemia. Fahraeus *et al*^17^ observed LDL-C at 2 months postpartum in healthy women (n=14) and the mean was 3.51 mmol/L. However, we are not aware of the results in the literature reporting SDs for the changes in LDL-C during breastfeeding for both women with and without FH.

A difference in LDL-C of 0.43 mmol/L (16.7 mg/dL) was shown to be associated with reduced occurrence of coronary heart disease in the IMPROVE-IT study.^18^ Thus, we consider a difference in LDL-C of 0.8 mmol/L to be a clinically relevant difference between the two groups (women with FH and control women) in changes from 2 to 4 weeks to 6 months postpartum. With a 5% level of significance, 80% power and a 2.5 ratio in sample size, we need 45 women with FH and 18 control women to observe a difference in changes of 0.8 mmol/L assuming an SD of 1.0 mmol/L in each group. Thus, we will include 50 women with FH and 20 control women.

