### Statistical analysis

Descriptive data will be expressed as mean (SD), median (IQR or min-max) or frequency (percentage). Mixed models for repeated measurements will be used to study the changes over time within and between the two groups. Missing data will be described, and mixed models for repeated measurements handle missing data.^19^ Potential confounding variables will be evaluated by directed acyclic graphs and included in the model. Depending on the amount of missing data in the confounding variables, multiple imputation will be considered.

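### The FH-control lipid contrast runs to 12 months without separating on-treatment from off-treatment values, so late differences can include drug effect

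*Protocol article*

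**What the plan says.** All references are to the protocol article.

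- **Primary outcome.** The comparison is introduced with "In women with FH compared with women without hypercholesterolaemia, we will investigate", and the change is measured "from 2 to 4 weeks post partum up to 12 months postpartum (absolute and relative change"). LDL-C is one of five lipids listed.
- **Introduction.** Lipid-lowering treatment is interrupted for conception, pregnancy and breastfeeding.
- **Breast milk samples.** Extra milk is collected on this condition: "If the women with FH (re)-start lipid-lowering treatment (eg, statin) while still having breast milk production". The abstract also plans for restart, and the secondary outcomes include drug concentrations after it.
- **Safety plan.** The V9 lipids of women with FH go to the GP or lipid-clinic physician "to ensure that the GP or treating physician will evaluate further treatment for the woman". No such step is described for controls.
- **Women without hypercholesterolaemia.** Known hypercholesterolaemia before pregnancy and a history of ASCVD exclude a woman from the control group.
- **Study visits and Table 1.** Blood is drawn from both groups at V0, V1, V3, V6, V9 and V12, and at VE1 and VE2 (1 and 2 months after weaning).
- **Statistical analysis.** "Mixed models for repeated measurements will be used to study the changes over time within and between the two groups". Missing data are left to the mixed model, and confounders are chosen with directed acyclic graphs.
- **Medical history, lifestyle factors and clinical examinations.** "At the first study visit, information on medical history, including FH diagnosis (age, genetic/clinical), lipid-lowering treatment history" is collected. Table 1 ticks medical history at V0 only. Study visits adds unspecified medical information at the main visits.

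**The concern.** Restart is a post-baseline event that the design expects in essentially one of the two groups. Weaning removes the stated reason for being off treatment, and the V9 letter prompts a treatment review before V12. If values before and after restart enter the model alike, the FH change is the postpartum fall plus drug effect, while the control change is the postpartum fall alone.

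A reader of the 12-month result could then conclude that LDL-C falls further after delivery in women with FH, when part or all of the difference is medication. The aim of relating breastfeeding to the lipid profile is exposed too, because weaning and restart tend to go together in FH women. Relative change gives no protection, since the drug effect is itself roughly proportional.

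**Working it through.** **1. The plan's own figure.** The article states "With a 5% level of significance, 80% power and a 2.5 ratio in sample size", and "45 women with FH and 18 control women to observe a difference in changes of 0.8 mmol/L assuming an SD of 1.0 mmol/L". For two means with allocation ratio k = 2.5:

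n(control) = (1 + 1/k) × (1.960 + 0.842)² × SD² / δ² = 1.4 × 7.849 × 1.0 / 0.64 = 17.2, rounded up to 18; n(FH) = 2.5 × 18 = 45.

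The figure reproduces as a two-sided calculation. It covers the change from 2-4 weeks to 6 months, not to 12 months.

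**2. Inputs for the drug effect.**
- FH LDL-C off treatment: 7.0 mmol/L, the 3-6 month mean from the cited pregnancy study (Sample size calculation). I assume it applies later in the year.
- r, the relative LDL-C reduction on treatment: not in the document; assumed 30-50%.
- p, the share of FH women on treatment at a visit: not in the document; assumed 10-50%.
- V1 is assumed to be off treatment in both groups, and controls untreated throughout.

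**3. Spurious difference when the true difference in change is zero:** p × r × 7.0 mmol/L.

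| Restarted | r = 30% | r = 40% | r = 50% |
|---|---|---|---|
| 10% | 0.21 | 0.28 | 0.35 |
| 25% | 0.53 | 0.70 | 0.88 |
| 50% | 1.05 | 1.40 | 1.75 |

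For scale, the spurious difference equals 0.8 mmol/L when p = 0.8 / (7.0 × 0.30) = 38%, or p = 0.8 / (7.0 × 0.50) = 23%.

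**4. Effect on a significance test.** The SD of change in the FH group becomes √(1 + p(1−p)(7.0r)²), carrying the 6-month SD of 1.0 over to 12 months. With 50 FH women and 20 controls, SE = √(SD²/50 + 1/20). Take p = 25% and r = 40%:
- SD = √(1 + 0.1875 × 7.84) = 1.57
- SE = √(2.47/50 + 0.05) = 0.315
- z = 0.70 / 0.315 = 2.22
- chance of a two-sided 5% result = about 60%, with no true difference

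Over the range in the table this chance runs from about 12% (p = 10%, r = 30%) to nearly 100% (p = 50%, r = 50%).

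**5. Does existing wording deal with it?** The missing-data sentence does not, because on-treatment values are observed. Adjustment for confounders does not clearly do so either: restart follows from FH status and lipid level, and occurs essentially in one group. A covariate would not settle which change is being estimated.

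**The case against.** The strongest reply is that the article is silent rather than wrong. The statistical section is short, and handling of treatment started after baseline is ordinary analysis-plan content that may exist elsewhere. Change regardless of treatment is also a legitimate descriptive target. This stands in part: the detail could be written elsewhere, and the all-samples estimate has a place. It does not remove the point, because the article itself fixes the 12-month window and builds in an FH-only treatment review at 9 months. Together with the model as described, these give a late contrast that mixes two effects.

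Several stronger readings are tempting and are not supported:

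- *The plan keeps every sample.* No sentence says so. The text only fails to separate the two kinds of value.
- *Treated samples cannot be identified.* Medical information is collected at main visits, and milk sampling on days 0-3 after statin initiation requires a known start date in women who restart while lactating. Capture is unspecified, not shown to be absent.
- *VE1 and VE2 bias the primary outcome.* They are not named as primary time points, and nothing says that treatment resumes exactly then.
- *The sample size contrast is undermined.* The V9 letter comes after 6 months and cannot affect it. Only women who wean early could restart in time, and no share is given.
- *Controls never start treatment.* This is a strong inference from the entry exclusions, not a stated fact.

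**Conclusion.** The concern holds for the later part of the primary window: mainly after 9 months, and earlier for women who wean early. The direction is the firm part. If V1 is off treatment and controls stay untreated, restart makes the FH fall look larger than it is. The size is conditional: 0.21-1.75 mmol/L under the assumed reduction and restart shares, neither of which the document supplies. The comparison with 0.8 mmol/L shows only that the possible bias is of the order the investigators call clinically relevant. It does not invalidate the 45/18 calculation.

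**What to change.** - Define the primary FH-control contrast on samples taken before any lipid-lowering (re)start. Treat later FH values as missing in the mixed model, under missing at random given earlier lipids. The V9 values that inform the treatment review are themselves in the model, which helps that assumption but does not guarantee it.
- Report all samples regardless of treatment as a sensitivity analysis, labelled as such.
- State explicitly that the current lipid-lowering drug and its start date are recorded at every main and additional visit.
- If VE1 and VE2 are used to describe a weaning effect, restrict that analysis to women who have not yet restarted.

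The cost is a paragraph of analysis wording and one medication question per visit. Fewer FH samples will support the estimates at 9-12 months, so these will be less precise and lean more on the missing-at-random assumption. If many women restart, few untreated FH women may remain at V12. No change to clinical management is implied, and the V9 letter stays as it is.

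### The primary outcome is five lipids on two scales over the first year, but the stated 5% level and 80% power belong to one part of it: absolute LDL-C change to 6 months

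*Protocol article*

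**What the plan says.** The Primary outcome section of the protocol article compares women with FH and women without hypercholesterolaemia on "The change in serum lipid profile (total cholesterol, LDL-C, high-density lipoprotein cholesterol (HDL-C), triglycerides, lipoprotein(a"), measured "from 2 to 4 weeks post partum up to 12 months postpartum (absolute and relative change"). That is five lipids and two scales over a period containing four main follow-up visits after V1 (V3, V6, V9, V12). None is marked as leading.

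The Sample size calculation section is narrower. It compares the two groups "in changes from 2 to 4 weeks to 6 months postpartum was performed for LDL-C (mmol/L) with 5% significance level and 80% power". The target is a difference of 0.8 mmol/L, and the result is that "we need 45 women with FH and 18 control women to observe a difference in changes of 0.8 mmol/L assuming an SD of 1.0 mmol/L", the same SD being taken for both groups. Enrolment is then set at 50 and 20. There is no calculation for the other four lipids, for relative change or for 12 months.

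The Statistical analysis section plans mixed models for repeated measurements, within and between groups, and does not pick out a contrast.

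**The concern.** A significance level and a power describe a particular test. Here they are given for one contrast, while the primary outcome contains many. Two consequences follow.

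- Any of the five lipids, on either scale, could be reported as the primary result. If each is tested at 5%, the chance that at least one is falsely significant exceeds 5%.
- The two scales can disagree. Women with FH start from much higher LDL-C, so the same proportional fall is a larger fall in mmol/L. With both scales primary, a finding that the groups differ and a finding that they do not could each be presented as the primary answer.

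A reader who sees 80% power beside this primary outcome may also take it to cover lipids and time points for which the article gives no SD and no target difference.

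**Working it through.** **1. Reproducing the stated sample size.** Inputs, all from the Sample size calculation section: difference 0.8 mmol/L, SD 1.0 mmol/L in each group, level 5%, power 80%, ratio 2.5. Sidedness is not stated. Two-sided is assumed because it reproduces the figures; one-sided gives 14 controls.

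Controls needed = (1 + 1/2.5) × [(1.960 + 0.842) × 1.0 / 0.8]² = 1.4 × 12.26 = 17.17, rounded up to 18. Women with FH = 2.5 × 18 = 45. This matches the article.

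Power from the noncentral t distribution, with noncentrality 0.8 / √(1/n₁ + 1/n₂):

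- 45 and 18: 0.8 / √(1/45 + 1/18) = 2.87 on 61 degrees of freedom; power 80.6%.
- 50 and 20: 0.8 / √(1/50 + 1/20) = 3.02 on 68 degrees of freedom; power 84.6%, if every woman contributes to the contrast.

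So the arithmetic is right for absolute LDL-C change to 6 months.

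**2. Does the choice of scale matter?** The same section quotes an earlier pregnancy cohort. LDL-C in women with FH was 8.6 mmol/L at week 36 and 7.0 mmol/L at 3–6 months postpartum; in women without hypercholesterolaemia it was 3.9 mmol/L at week 36.

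- Fall with FH: 8.6 − 7.0 = 1.6 mmol/L; 1.6 / 8.6 = 18.6%.
- An equal relative fall in controls: 0.186 × 3.9 = 0.73 mmol/L.
- Relative difference: zero. Absolute difference: 1.6 − 0.73 = 0.87 mmol/L, above the 0.8 mmol/L target.

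This is an illustration. The baseline is week 36, not 2–4 weeks postpartum, and the equal relative fall is assumed. It is plausible, because the Introduction says that the relative rise in pregnancy is similar in the two groups. It is not the only possibility: the other healthy cohort cited has a mean of 3.51 mmol/L at 2 months, and setting that against 3.9 across studies gives a fall of 0.39 mmol/L (10%), in which case the scales would agree in direction.

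**3. Chance of at least one false positive when each test uses 5%.** For k independent tests it is 1 − 0.95^k: 22.6% for k = 5 and 40.1% for k = 10. Lipids, and the two scales of one lipid, are correlated. The article gives no correlations, so a common value was assumed and varied (simulated normal statistics, 200,000 draws):

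| Assumed correlation | 5 tests (five lipids, one scale) | 10 tests (five lipids, two scales) |
|---|---|---|
| 0 (formula) | 22.6% | 40.1% |
| 0.3 | 20.8% | 35.1% |
| 0.5 | 18.3% | 28.7% |
| 0.8 | 12.8% | 17.2% |
| 0.9 | 10.1% | 12.7% |

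The ranges are about 10–23% and 13–40%. The independent-test figures are upper ends, above all for ten tests, since absolute and relative change in the same lipid are closely related.

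**4. What cannot be computed.** Power for the other lipids, for relative change and for 12 months, because the article gives no SDs or target differences for them.

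**The case against.** Sizing a broad outcome on one component is common, and the article says openly which component it used. The study is an observational cohort whose aims are to investigate and describe, and its size is set largely by how many pregnant women with FH can be found. Strict control of the overall error rate is debatable in such a study. These points stand, and they limit the finding. They do not remove it, because the article itself invokes a 5% test with 80% power and places that beside a primary outcome several times as wide.

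Three stronger readings are tempting, and the article supports none of them.

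- *That the two sections contradict each other.* They do not. Six months lies within the period up to 12 months, V6 is a main visit for both groups, and LDL-C is one of the five lipids. The sized contrast is a subset of the primary outcome.
- *That a multiplicity rule is missing.* A statistical analysis plan may exist and is not shown, so absence of a rule from a journal article is not a fault. The point is that the article's stated primary outcome and its stated calculation differ in scope.
- *That 40 contrasts will be tested (5 lipids × 2 scales × 4 visits).* The Statistical analysis section specifies no separate test at each visit. A single group-by-time test per lipid and scale would give ten. Separate visit tests would raise the false-positive chance further, but assuming them goes beyond the text.

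**Conclusion.** The point holds as a mismatch of scope. The 5% level and 80% power are correctly computed for absolute LDL-C change to 6 months and do not carry over to five lipids on two scales up to 12 months.

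Its size depends on assumptions that the article cannot settle. The false-positive ranges assume that each lipid is tested at 5%, with a common correlation between 0 and 0.9; across that whole range they stay at least twice the nominal level. The 0.87 mmol/L illustration assumes equal relative falls from week 36. It shows that the scale can decide the answer, not that it will.

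This should be corrected, but it does not undermine the design: enrolment is adequate for the contrast that was sized, under the article's own SD.

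**What to change.** By dated amendment and registry update, before the data are analysed:

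- Name one primary contrast: the difference between women with FH and controls in absolute LDL-C change (mmol/L) from V1 to V6, estimated from the planned mixed model.
- Make total cholesterol, HDL-C, triglycerides, lipoprotein(a), relative change and the course to 12 months secondary, reported with confidence intervals and without confirmatory claims.
- State in the Sample size calculation section that the 80% power applies to the named contrast only.

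No visit, sample or enrolment target changes. The cost is more than wording: inclusion began in June 2022 and the study is registered, so the change must be dated and justified. The other lipids, the relative scale and the 12-month course lose primary status, although the first-year course, which is the overall aim, is still reported.

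Keeping all five lipids primary is possible but costs power. With the 5% split equally over five lipids (1% each), power for the LDL-C contrast with 50 and 20 women falls from 84.6% to 64.6%; split over five lipids and two scales (0.5% each), it falls to 55.1%. The article proposes no such split; the figures only show what that alternative would cost.
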